## Abstract

**Introduction:**

Growing research suggests that dementia is a complex disorder with multiple risk factors and causes. The Finnish Geriatric Intervention Study to Prevent Cognitive Impairment and Disability (FINGER) demonstrated that lifestyle interventions could confer cognitive benefits. Inspired by this, the GOIZ-ZAINDU (GZ) feasibility study adapted the FINGER approach to the Basque context. Building upon the GZ study, the CITA GO-ON trial aims to enhance and expand the evidence supporting dementia prevention through a multidomain intervention of risk factor management and resilience promotion.

**Methods:**

It is a two-year, population-based, randomized controlled trial to prevent cognitive decline in adults aged 60–85 years with Cardiovascular Risk Factors, Aging and Dementia (CAIDE) risk score ≥6, no dementia, and below-than-expected performance on at least one of three cognitive screening tests. Participants are randomized (1:1) to receive either Regular Health Advice (RHA) or a Multidomain Intervention (MD-Int) that encompasses cognitive training, socio-emotional skills, multicomponent physical exercise, nutritional and culinary intervention, and monitoring for cardiovascular risks, pharmacological drug mismanagement, and comorbidities. The primary outcome is the efficacy of the intervention to reduce the risk of cognitive decline measured by the global composite *z*-score of the modified Neuropsychological Test Battery over two years. The secondary outcomes measure cost-effectiveness, quality of life, and functional abilities. Blood samples and brain imaging will also be collected to evaluate the effects of the intervention on brain structure and plasma biomarkers.

**Results:**

Recruitment has been completed with 1051 participants selected (mean age (standard deviation, SD) of 69.65 (6.36), 58,50 % female, and mean CAIDE (SD) of 7.62 (1.427). The final participant is expected to complete the last study visit by the autumn of 2026.

**Discussion:**

The CITA GO-ON Study, as a part of the World-Wide FINGERS network, is designed to validate the efficacy of a multidomain lifestyle intervention for dementia prevention and contribute valuable data to inform public health strategies fostering healthy, active aging.

## Background

1

Dementia and late-life cognitive impairment impose significant disability and degradation of the quality of life for both affected individuals and their caregivers, leading to elevated social and healthcare expenditures. The global number of persons with dementia has doubled in recent years (GBD 2016 Dementia Collaborators, 2019), and forecasting models project a marked escalation in dementia cases if effective preventive measures are not established (Soto-Gordoa et al., 2015).

Investigations into dementia and neurodegenerative conditions have uncovered a multitude of underlying coexisting comorbidities, particularly in older populations (Larson et al., 2013; Wu et al., 2017). In addition, a spectrum of lifestyle factors has been identified as influential in the risk trajectory for cognitive decline throughout life (Norton et al., 2014). Observational studies have reinforced that addressing traditional cardiovascular risk elements, such as hypertension, obesity, and diabetes, may delay the onset of cognitive deficits (Kemppainen et al., 2018; O’Brien et al., 2019; Dhana et al., 2020). A cognitively and physically active lifestyle is associated with healthy cerebral aging. Recent insights also revealed that deficits in social engagement and emotional well-being may contribute to the emergence of cognitive impairment (Fratiglioni et al., 2020; Lisko et al., 2021; Röhr et al., 2023). The multifactorial nature of cognitive decline suggests that interventions targeting a combination of lifestyle and health factors might offer superior preventive capability (Solomon et al., 2013; Kivipelto, 2016). While some pharmacological trials have shed light on the treatment of Alzheimer’s dementia (Mintun et al., 2021; van Dyck et al., 2022), a significant number have not successfully demonstrated efficacy in delaying cognitive decline (Kivipelto et al., 2018a), highlighting the need for complementary nonpharmacological strategies for both primary and secondary prevention. The Lancet Commission on Dementia Prevention, Intervention, and Care underscores the importance of initiatives that promote lifestyle alterations and mitigate dementia risk factors in midlife and beyond (Livingston et al., 2020).

The Cardiovascular Risk Factors, Aging, and Dementia (CAIDE) risk score (Kivipelto et al., 2006) is a well-known and validated tool that can predict cognitive trajectories. The Finnish Geriatric Intervention Study to Prevent Cognitive Impairment and Disability (FINGER) trial (Ngandu et al., 2015) is a large-scale investigation that substantiates the cognitive benefits of a multidomain lifestyle intervention for older adults at elevated risk of dementia, as determined by the CAIDE dementia risk score (Ngandu et al., 2014). Other similar multidomain interventions, such as the Multidomain Alzheimer Preventive Trial (MAPT) (Andrieu et al., 2017) and Prevention of Dementia by Intensive Vascular Care (van Charante et al., 2016) (preDIVA) studies, yielded positive outcomes within participant subgroups characterized by higher CAIDE risk scores or those with cerebral amyloid deposition. The World-Wide FINGERS network (Kivipelto et al., 2020) was established to advance scientific substantiation of this complex domain. This initiative is dedicated to enhancing protocol standardization and facilitating data exchange to bolster research efficacy.

In the spirit of the pioneering FINGER study, the CITA-alzheimer research team group applied the CAIDE dementia risk score in non-demented longitudinal cohorts and population-based investigations (Ecay-Torres et al., 2018). Our findings revealed that diminished cognitive performance was correlated with CAIDE risk score, vascular, amyloid, and neurodegenerative biomarkers in asymptomatic at-risk adults. Recently, our team embarked on a feasibility study called the GOIZ ZAINDU (GZ) trial (Tainta et al., 2024a), which adapted the FINGER multidomain lifestyle intervention model to the cultural, healthcare, and social frameworks of the Basque region. Adherence to the intervention program and integration with existing health system protocols were pivotal in attaining the primary objective. Efficacy analysis revealed a significant less decline in executive function and processing speed in the multidomain intervention (MD-Int) group. These pilot findings laid the groundwork for a comprehensive efficacy trial, the “CITA GO-ON” study, registered with ClinicalTrials.gov (NCT04840030). This trial encompasses older adults approaching cognitive decline, characterized by an augmented dementia risk as assessed by the CAIDE score manifesting either suboptimal performance in brief cognitive evaluations or persistent memory complaints (Figure 1).

**Figure 1 fig1:**
[figure not shown]
CITA GO-ON study target population.

The primary objective of the CITA GO-ON study is to evaluate the efficacy of a multidomain lifestyle intervention as a preventive strategy against cognitive decline. Concurrently, this study will establish a repository of brain imaging and biomarker data, facilitating exploratory research on the physiological impacts of lifestyle modifications in the adult population. This paper delineates the principal protocol of the CITA GO-ON study, outlines the methodology used for participant recruitment, and provides an update on the current status of the study plan.

The success of the FINGER trial may be attributed to the meticulous selection of participants.

This encompasses an evaluation of the intervention cost-effectiveness and its potential integration into public health frameworks aimed to promote healthy and active aging, as well as dementia prevention.

This hypothesis is based on the premise that such interventions attenuate modifiable risk factors and generate positive neuroplastic changes, as demonstrated by brain imaging and biomarker profiles. These results are expected to be attained at an acceptable cost-effectiveness to ensure the public health utility of the intervention in promoting healthy aging and dementia prevention.

The central hypothesis of the CITA GO-ON study postulates that a multidomain lifestyle intervention over 2 years in older adults at high risk for dementia is significantly efficacious to reduce the risk of progression to cognitive decline.

## Materials and methods

2

### Study design

2.1

The CITA GO-ON study is a single-center, population-based, randomized controlled two year trial to evaluate the efficacy of a multidomain lifestyle and vascular risk factor intervention in averting cognitive decline.

### Study objectives

2.2

The primary objective is to ascertain the efficacy of the intervention to attain a 20% reduction in the proportion of subjects exhibiting a decline in cognitive performance, as measured by the change in the global cognition z-score on the modified Neuropsychological Test Battery (mNTB) (Harrison et al., 2007; Kivipelto et al., 2013), between baseline and 24 month visits in the multidomain intervention group (MD-Int) relative to the regular health advice (RHA) group. Secondary objectives include: (1) analyzing the cost-effectiveness of the intervention; (2) determining the beneficial effects of the intervention on functional abilities, quality of life, and symptoms of depression and anxiety; and (3) investigating the impact of lifestyle interventions on: neuroimaging parameters of brain volumetry, white matter integrity and vascular burden; plasma biomarkers of Alzheimer’s pathology, neurodegeneration, and neuroinflammation; epigenetic marks; lipid dysregulation; and cognitive and brain reserve capacity.

### Study participants

2.3

Eligible participants are non-demented older adults aged 60–85 years who are willing and able to engage with all study evaluations and interventions, have a CAIDE dementia risk score of 6 or higher, and score below the established cutoff points in at least one of three brief cognitive evaluations: Fototest score ≤ 35, Memory Alteration Test (T@M) score ≤ 40, (Carnero-Pardo and Montoro-Ríos, 2004; Rami et al., 2007; Tainta et al., 2024b), or score ≥20 on the first 12 items (episodic memory) of the Cognitive Change Index (CCI) self-report version (Saykin et al., 2006; Risacher et al., 2017). The exclusion criteria, detailed in Supplementary Table S1, comprise conditions that may hinder the attainment of study goals, adherence to procedures, as well as specific clinical conditions that could by themselves compromise cognitive performance.

### Ethical approval and consent to participate

2.4

This study was approved by the Euskadi Drug Research Ethics Committee (CEIm-E) (ID: PI2020244). This randomized trial is been conducted following the Consolidated Standards of Reporting Trials guidelines (CONSORT) (Schulz et al., 2010). All participants provide written informed consent. Samples obtained and unanalyzed will be stored as biological samples after the corresponding informed consent is signed. Explicit consent for the publication of the study results and experience was obtained from each participant.

### Screening period

2.5

The recruitment approach was community focused in Gipuzkoa, Spain. The primary recruitment strategy includes collaboration with local town halls and community services supported by press releases, social media campaigns, direct mailings, and community talks. Broad outreach efforts employ mass mailing to the target age demographics, local advertisements at bus stops, billboards, and local publications. This initial marketing phase was augmented with informative sessions conducted at neighborhood associations. Comprehensive study information and access to informed consent documents are available on the study website^1^.

#### Prescreening

2.5.1

Persons interested fill out an online form that allows the identification of those who meet the pre-established requirements before attending an individualized face-to-face screening visit.

For the online pre-screening procedure interested participants access a web-based formulary [Research Electronic Data Capture (REDCap)-based; Harris et al., 2008, 2018] to collect basic sociodemographic data, a standardized questionnaire that allows to estimate a CAIDE dementia risk score and the presence of exclusion criteria (Table 1). Prior to the fulfillment of the on-line form (Supplementary Table S2), participants receive detailed information on the study objectives, future activities, and evaluations.

**Table 1 tab1:** Variables at prescreening and screening visits.

Screening variables		Prescreening (virtual evaluation)	Screening (face-to-face evaluation)
	Time for randomization visit	- 36 weeks	- 24 weeks
Personal data	Contact information	x	
	Sociodemographic data	x	
	Habit of using the internet and virtual communication tools.	x	
Dementia risk score	CAIDE	x	x
	Inclusion/Exclusion criteria	x	x
	Informed consent		x
Screening tools	Cognitive Change Index	x	
	Barthel index		x
	Geriatric Depression Scale		x
	Fototest, T@M		x
Physical condition	Anthropometry and cardiovascular risk evaluation		x
Medical history	Self-reported impairments and symptoms		x
	Reported medical conditions and current medication: information from participants’ GGPregarding current diagnoses, medication and lab values, vascular risk factors, and smoking habit.		x

#### Screening visit

2.5.2

Participants with an estimated CAIDE dementia risk score ≥ six and no reported exclusion criteria are invited for an in-person selection evaluation visit and full written information is provided. At the beginning of the interview, information regarding the study details is provided to all participants. After reading the informed consent form and solving all possible questions and doubts, participants sign an informed consent. Subsequently, past medical history is recorded to rule out exclusion criteria. Demographic and anthropometry data together with cholesterol determinations are collected and a current CAIDE dementia risk score is obtained. Brief cognitive testing is then administered and CCI scores are accounted for to complete inclusion/exclusion criteria accomplishment. The variables obtained at the screening visit are depicted in Table 1.

### Baseline evaluation

2.6

The recruitment period is defined as the time between the prescreening and the randomization visit (Figure 2). The CITA GO-ON study assessments and the corresponding schedule and procedures are detailed in Tables 2, 3. All participants complete the Baseline, 12-month, and 24-month visits for primary and secondary efficacy variables. In participants who consent, biological samples and neuroimaging (3T MRI) data are collected at baseline and 24-month follow-up visits.

**Figure 2 fig2:**
[figure not shown]
Timeline of the CITA GO-ON study periods. *Blood sample collection and neuroimaging acquisition are conducted in a subgroup of participants who have consented to it.

**Table 2 tab2:** CITA GO-ON study assessments.

Primary outcomes	
Cognitive performance I	Modified Neuropsychological Test Battery (global composite z scores)
Secondary outcomes	
Cognitive performance II	mNTB specific cognitive domains: episodic memory, executive function, and processing speed.
Functional independence	Amsterdam Questionnaire for Instrumental Activities of Daily Living
Quality of Life	EuroQoL-5D
Psychological and behavioral eval. I	Goldberg Anxiety and Depression Scale (GADS)
Exploratory variables	
Cognitive performance III	Leisure and productive activities questionnaire. Visual Perception and Construction composite.
Socioemotional evaluation	Physiological stress (Heart rate variability, EMWAVE); Emotional attention; Emotional understanding; Emotional regulation (TMMS-22 Old); Mindful Attention Awareness Scale (MAAS; Barajas and Garra, 2014); Subjective perception of loneliness (Velarde-Mayol et al., 2016) (UCLA); Satisfaction with Life Scale (Pons et al., 2000) (SWLS).
Nutritional evaluation I	Mediterranean Diet Adherence Screener (Schröder et al., 2011) (MEDAS) questionnaire
Nutritional evaluation II	Food Frequency Questionnaire(de la Fuente-Arrillaga et al., 2010) (FFQ); Home Cooking Frequency Questionnaire (Goni et al., 2022) (HCFQ),
Physical activity and exercise eval. I	SPPB (Short Physical Performance Battery), Six meters walking speed
Physical activity and exercise eval. II	Dual-task 6 meters walking speed, 30” Chair stand test, Handgrip test and step up and go tests (recorded at basal visit, 12-month visit and the end of the study). Daily physical activity is measured by steps or meters per day.
PHYSICAL and METABOLIC CONDITION	Anthropometric measure (height, weight, calculation body-mass-index and waist and hip perimeter), blood pressure, glucose levels, total cholesterol.
Brain MRI	Structural and DTI imaging
Blood samples	Blood sample for plasma biomarkers and DNA extraction.
Cognitive performance IV	Cognitive Reserve Questionnaire (Rami et al., 2011); Bilingualism questionnaire (https://sites.la.utexas.edu/bilingual/)
Safety variables	
Adverse events evaluations	
Information from participants GP regarding current diagnoses and medication and lab values (blood count, cholesterol, glucose, renal and liver function, thyroid hormones, B12 vitamin, folic acid)	
Other control variables	
Psychological and behavioral eval. II	Perceived Stress (Levenstein et al., 1993) (PSQ), and sleep quality (Pittsburgh Quality of sleep scale).
Use of e-health systems to track health habits	

**Table 3 tab3:** CITA GO-ON study visits assessments.

Variables	Baseline evaluation	Randomization	v1	v2	v3	v4	v5	v6
Time from randomization visit	-12 weeks	0	4 months	8 months	12 months	16 months	20 months	24 months
Visit time window	+/− 30 d.		+/− 20 d.	+/− 20 d.	+/− 20 d.	+/− 20 d.	+/− 20 d.	window of 90 d.
Primary outcomes								
Cognitive performance I	x				x			x
Secondary outcomes								
Cognitive performance II	x				x			x
Functional independence	x				x			x
QoL	x				x			x
Psychological and behavioral eval. I and II	x				x			x
Exploratory variables								
Cognitive performance III	x				x			x
Socioemotional evaluation	x				x			x
Nutritional evaluation I	x				x			x
Nutritional evaluation II	x							x
Physical activity and exercise eval. I	x				x			x
Physical activity and exercise eval. II	x				x			x
PHYSICAL and METABOLIC CONDITION	x				x			x
Brain MRI	x							x
Blood samples	x							x
Cognitive performance IV	x							
Safety variables								
Adverse events evaluations	x				x			x
Information from participants GP regarding current diagnoses and medication and lab values.	x							x
Intervention group-specific variables								
Nutritional evaluation I			x	x		x	x	
Physical activity and exercise eval. I			x	x		x	x	
PHYSICAL and METABOLIC CONDITION			x	x		x	x	

#### Primary outcome: cognitive performance I

2.6.1

In accordance with the WWFINGERS network data harmonization recommendations, cognitive performance change is the primary outcome. It is assessed using the modified Neuropsychological Test Battery (mNTB) (Harrison et al., 2007), previously described for in our pilot study (Tainta et al., 2024a) and in Supplementary Table S3. It is recorded by trained neuropsychologists who are blinded to the group assignment at baseline evaluation and at the 12-month and 24-month visits. The mNTB Cognitive Global score is obtained. Composite cognitive z-scores are calculated based on the results of all single tests. The higher the score, the better the performance. Changes in global cognition are assessed by differences between Global Cognitive composite z-scores at baseline and 24-month visits.

#### Secondary outcome assessments

2.6.2

*Cognitive Domains – (cognitive performance II):* mNTB executive function, Memory, and Processing speed scores are obtained. Apart from the mNTB scores, perception and construction abilities function composites are also assessed using the Judgement Line Orientation, Rey Complex Figure copy, and 15 object test. Differences in pre-and post-intervention scores in mNTB-episodic memory, mNTB-executive function, and mNTB-processing speed z-scores together with perception and construction abilities composites are used to assess changes in specific cognitive domains.*Functionality:* The Amsterdam Questionnaire for Instrumental Activities of Daily Living (A-IADL-Q) (Jutten et al., 2017) serves to assess the impact of the intervention on an individual’s functional capacity.*Quality of life:* The EuroQoL-5D (Kind et al., 1998) formulary evaluates participants’ quality of life.*Affective and behavioral evaluation:* The Goldberg Anxiety and Depression Scale (Goldberg et al., 1988) has been incorporated into the study design to evaluate the influence of the intervention on the symptoms of depression and anxiety.

#### Exploratory assessment

2.6.3

A comprehensive assessment of the socioemotional domain, dietary and culinary habits, physical fitness, and vascular risk factors have been devised to evaluate the impact of the multidomain intervention (Table 2).

**Neuroimaging collection:** Subjects who consent will undergo a brain MRI during Baseline and 24-month visit evaluation to evaluate brain volume trajectories, cortical thickness, and white matter changes (MRI). MRI sequences are listed in Table S4.**Biological sample collection and banking:** Biological samples are collected, processed, and stored at Baseline and at 24-month visits to evaluate the effect of the intervention on plasma biomarkers. Whole blood, buffy coats, plasma, and serum are collected in polypropylene tubes, transferred onto polypropylene cryovials, and immediately stored at-80°C for future analysis after centrifugation. The analyses for plasma AT (N) biomarkers will be performed on a SiMoA (Single Molecule Array) platform using commercial kits from Quanteryx APOE genotyping: APOE gene will be genotyped by Restriction Fragment Length Polymorphism (RFLP) technique (DNA amplification, specific primers, PCR, and enzymatic restriction with CfoI enzyme). Stool samples for microbiome analysis will also be collected.

#### Safety assessments

2.6.4

Participants provide information on past medical history and current illnesses, which is confirmed through their clinical history obtained from their General Practitioners (GPs) at the beginning of the study period and follow-up visits. Any change in a participant health along the study is recorded as an adverse event. Adverse events are actively identified through structured interviews at every follow-up visit. Current diagnoses, medication, and lab values, including blood count, cholesterol, glucose, renal and liver function, thyroid hormones, B12 vitamin, and folic acid, are documented before randomization.

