#### Group 1—RHA group

2.7.2

Participants assigned to the RHA group undergo follow-up evaluations at 12-month and 24-month marks. Adherence to the lifestyle recommendations provided during the randomization visit is self-directed, with no additional guidance on the activities pursued to follow these recommendations. Participants may connect with other healthcare professionals, including their general practitioners, who are not part of the study team according to their individual health needs.

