#### Group 2—MD-Int group

2.7.3

The MD-Int program represents an update of the GZ pilot study intervention program, introducing a socio-emotional component along with a greater frequency of visits and extended materials within each intervention domain. The program aims to promote healthy brain aging, provide tools for incorporating these routines into daily life, and strengthen the social environment. The program is tailored to each participant needs and abilities throughout the study. Apart from the 12-month and 24-month visits participants in the MD-Int group receive individual interviews with the study physician and physiotherapist every 4 months. In these visits cardiovascular and metabolic parameters (blood pressure, pulse, weight, BMI, hip and waist perimeters, capillary glucose, and cholesterol), Mediterranean diet adherence, physical capacity and activity, active medications and adverse events are reviewed and monitored.

The MD-Int program is administered in small groups of 10–15 participants, with a designated investigator or “group leader” overseeing the various MD-Int activities and intervention staff. Intervention components are listed in Table 4. Cognitive stimulation intervention comprises 16 group sessions in workshops (24 h) conducted by a neuropsychologist and over 100 h of individual at-home cognitive training exercises using the EXERCITA® program that was specifically designed after the pilot study. Nutritional and culinary intervention includes eight nutritional and show cooking workshops facilitated by study nutritionists and professional chefs. Individual recommendations for physical exercise based on the VIVIFRAIL©^2^ multicomponent physical exercise tool. And finally, up to 16 group workshops focused on promoting socio-emotional skills the intervention.

**Table 4 tab4:** Description of CITA GO-ON MD-Int components.

Intervention component	Description

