Socioemotional intervention	This branch focuses on emotional well-being by fostering awareness, communication, and regulation of emotions. This is achieved by emphasizing emotional intelligence and the cognitive impact of emotions. This program encompasses six key modules: psychoeducation, emotional awareness, emotional communication, emotional management, coping with loneliness, and promotion of subjective well-being. The intervention will be implemented in 16 group sessions scheduled, along with cognitive intervention workshops. The group work is complemented by a homework assignment designed to integrate the session’s concepts into participants’ daily lives. Socioemotional intervention plays a transversal role in multicomponent interventions, enhancing social commitment, motivation, and adherence to the program.
Cardiovascular risk factor and comorbidities intervention	Every 4 months, the study team will evaluate the participants for cardiovascular risk factor check-ups, including measurements of blood pressure, weight, capillary blood glucose, and cholesterol levels. If the evaluation suggests the emergence of a new risk factor or poor control of a known risk factor, the primary care physician will provide appropriate advice and recommendations for the management, initiation, or adjustment of pharmacological treatments. Additionally, at each visit, the patient’s active medications will be reviewed following the current guidelines for minimizing inappropriate medications from the Basque Public Health System (http://www.osakidetza.euskadi.net/cevime, Vol 20 n° 8, 2012).

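### The adverse-event rule in section 2.6.4 takes in any change in health, so the resulting count cannot be read as a measure of harm

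*Protocol article*

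**What the plan says.** Section 2.6.4 (Safety assessments) gives the recording rule: "Any change in a participant health along the study is recorded as an adverse event". It then says how events are found: "Adverse events are actively identified through structured interviews at every follow-up visit". The sentence before the rule concerns medical history and current illnesses, confirmed through general practitioners' records.

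Section 2.7.2 sets the control schedule: "Participants assigned to the RHA group undergo follow-up evaluations at 12-month and 24-month marks". Section 2.7.3 says that "participants in the MD-Int group receive individual interviews with the study physician and physiotherapist every 4 months". Those interviews cover "cardiovascular and metabolic parameters (blood pressure, pulse, weight, BMI, hip and waist perimeters, capillary glucose, and cholesterol", together with diet and physical capacity, and at them "active medications and adverse events are reviewed and monitored". Table 4 adds a medication review at each visit and a route to changes in drug treatment: "If the evaluation suggests the emergence of a new risk factor or poor control of a known risk factor, the primary care physician will provide" advice on management.

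Table 2 puts the cognitive battery under primary and secondary outcomes, and anthropometry, blood pressure, glucose and cholesterol under exploratory variables. The line "Adverse events evaluations" stands under safety variables. Table 3 marks that line at baseline, 12 and 24 months and not in its MD-Int-specific block, which does not agree with the four-monthly review in section 2.7.3.

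**The concern.** An adverse-event definition normally carries a direction: the occurrence is unfavourable, and it is new or worse than at the reference point. This one has neither element. Any change qualifies, at any point in the study.

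That matters more here than in most trials, because MD-Int exists to change health. On the wording, intended weight loss, a fall in blood pressure, or the withdrawal of an inappropriate medicine after review is an adverse event. So is cognitive decline or a new diagnosis of mild cognitive impairment (MCI) or dementia, which overlaps what the trial measures as efficacy. A count built this way adds three different things together. It could suggest harm where there is none, or hide a real harm behind fewer cognitive events. At stake is any safety summary the trial reports. The primary efficacy analysis is not affected.

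**Working it through.** The article states no adverse-event rate, safety hypothesis or safety test, so there is no figure to reproduce. The check has four steps.

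**1. What the rule takes in.** Common kinds of change, set against the article's own classification:

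| Change during follow-up | Under 2.6.4 as worded | Where the article otherwise places it | What it represents |
|---|---|---|---|
| New or worse illness | Adverse event | Safety variables (Table 2) | Possible harm |
| Intended fall in weight, blood pressure, glucose or cholesterol | Adverse event | Physical and metabolic condition, exploratory (Table 2) | Benefit |
| Medicine stopped or adjusted after review | Adverse event, if read as a change in health | MD-Int component (Table 4); practitioner information (Table 2) | Intended action |
| Fall in the cognitive composite | Adverse event | Primary outcome (Table 2; 2.10.5) | Efficacy |
| New MCI or dementia | Adverse event | No row of its own in Table 2 | Efficacy-related |

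Only the first row is a safety signal in the usual sense.

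**2. Direction if decline is counted.** Inputs: planned proportions declining over two years, 49% in RHA and 32% in MD-Int (2.10.1); numbers allocated so far, 465 and 455 (section 3). Section 2.10.5 defines decline as any fall in the composite from baseline to 24 months.

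- RHA: 0.49 × 465 = 227.85, about 228 participants.
- MD-Int: 0.32 × 455 = 145.6, about 146 participants.
- Ratio of proportions: 0.32 / 0.49 = 0.65. Difference: 49 − 32 = 17 percentage points, with the excess in RHA.

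Now suppose only declines and favourable changes are counted, each participant at most once. MD-Int would then show a net excess only if participants recorded solely for a favourable change were more than 17 points more frequent there than in RHA. In MD-Int that is 0.17 × 455 = 77.35, about 77 participants beyond the RHA rate. The article gives no figure from which to judge this.

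**3. The fully literal case.** Weight, blood pressure and a composite score almost never repeat exactly. If every movement up or down counted, nearly every participant in both arms would have an event. The proportion with an event would then be uninformative, not biased one way.

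**4. Visits, for the recode.** MD-Int is seen at months 4, 8, 12, 16, 20 and 24 (six contacts), and RHA at months 12 and 24 (two). An entry dated month 4, 8, 16 or 20 therefore identifies MD-Int. Unequal frequency of asking is a separate problem: equal schedules would not repair the definition, and a better definition would not equalise the schedules.

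**The case against.** The strongest reply is context. The rule sits under a safety heading, directly after a sentence on illnesses confirmed by practitioners, so new or changed illness is probably what was meant. Table 2 already keeps cognition, metabolic measures and adverse events in separate classes, and section 2.7.3 names them as separate items. Nothing in the article says that weight loss or a change in test score has been entered as an adverse event. A journal article also condenses a fuller protocol, which may hold the working definition. Finally, wide capture does not prevent later classification.

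Much of this stands, and it makes actual damage less certain. It does not remove the point. The article does not leave the definition out; it states one, and the stated one lacks the limit that the context only suggests. The separate classes in Table 2 do not say that a change recorded there is excluded from the adverse-event record.

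A reader might go further and infer that the rule will produce a false appearance of harm in MD-Int. The documents do not support that. Step 2 shows that counting decline points to RHA. Control participants also receive lifestyle advice (2.7.1) and may see their own practitioners (2.7.2), so favourable changes would not be confined to MD-Int. The Table 4 text on new or poorly controlled risk factors concerns unfavourable changes. No between-arm comparison of adverse events is described: section 2.10.5 covers baseline, efficacy and secondary outcomes. Any p-value for a spurious excess would rest wholly on assumed increments.

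**Conclusion.** The point holds as a defect of definition. As worded, section 2.6.4 yields a count that mixes harm, benefit and efficacy and cannot be interpreted as safety in either direction. The size and sign of the net effect cannot be derived from the article. The one component that its own figures allow, cognitive decline at the planned 49% and 32%, would put the excess in RHA (about 228 against 146), on the assumption that falls in the composite are entered as adverse events. Whether improvements or test scores have been so entered is not known.

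The consequence is limited to safety reporting, and confidence is moderate because the full protocol may already contain a proper definition. The correction is still worth making now: the last visit is expected in autumn 2026, so entries are still being collected.

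**What to change.** - Replace the sentence in section 2.6.4 with a definition: an adverse event is any untoward medical occurrence that is new or worsened after randomization.
- State that intended or favourable changes in weight, blood pressure, glucose, cholesterol and medication are recorded only under their own Table 2 variables.
- State that cognitive decline, MCI and dementia are tabulated as study outcomes, separately from the adverse-event count and by arm, so that they are kept and not counted twice.
- Recode existing entries to this definition blind to arm, with visit dates masked because month 4, 8, 16 and 20 entries reveal MD-Int.
- Reconcile section 2.7.3 with Table 3 on the visits at which adverse events are assessed.
- If the full protocol already has such a definition, cite it and correct the article's sentence.

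The cost is a short text change and some data-management time for the recode, which depends on existing entries being described well enough to classify.
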